##### GnRH-ant protocol control group

2.2.1.2

COH would be performed by a fixed GnRH-ant protocol. The patients would receive COH from day 2 or 3 of menstruation. The selection and adjustment of Gn and the treatment of slow ovarian response would be the same as those in the depot GnRH-a protocol group. During COH, any other adjuvant drugs are not allowed. On the 5th or 6th day of COH, 0.25mg cetrorelix acetate (Cetrotide ^®^, Merck Serono, Germany) or ganirelix acetate (Orgalutran^®^, Organon, USA/QingLe^®^, CHIA TAI TIANQING, Lianyungang, China) would be injected subcutaneously into the trigger every day. rHCG (Ovidrel^®^, Merck Serono, Germany) trigger would be used if the patient is not at high risk for OHSS. If the patient is at high risk for OHSS (trigger day E2≥5000pg/ml or ≥18 follicles with a diameter larger than 14mm), 0.2mg GnRH-a (Decapeptyl^®^, Ferring, Switzerland) or HCG 2000IU combined with 0.2mg GnRH-a (Decapeptyl^®^, Ferring, Switzerland) would be used for trigger. Other medications are at the discretion of the attending doctor.

##### GnRH-ant protocol plus GH intervention group

2.2.1.3

Based on the GnRH-ant protocol control group, all patients will receive subcutaneous injection of 5IU GH (Genescience Pharmaceutical, Changchun, China) once a day from the beginning of COH until the trigger day.

#### Oocytes pick-up and embryo transfer

2.2.2

Oocytes would be picked up 36-38 hours after the trigger. During the OPU, follicular fluid from dominant follicles (diameter ≥18mm, oocytes visible under microscopy) that are not contaminated by blood would be collected, centrifuged, and stored in a -80°C refrigerator. The remaining follicular fluid and follicular flushing fluid would be collected in 50ml centrifuge tubes, and granulosa cells would be separated and extracted by enzymolysis method, and stored at -80°C in the refrigerator. 16-18 hours after insemination, the embryonic pronucleus (PN) would be observed. The embryos would be observed on day 3 after insemination. High-quality embryos were defined as 7-10 cell stage embryos of 2PN origin with blastomere fragments ≤20% at day 3 after fertilization (22). For patients meeting the criteria of fresh embryo transfer, one day 3 high-quality embryo would be transferred, and all remaining embryos would be cultured to blastocyst stage and frozen. For patients who need to cancel fresh embryo transfer due to various reasons (**Table 2**), 0-1 day 3 high-quality embryos would be frozen according to the embryo condition, and the remaining embryos would be cultured to the blastocyst stage and frozen.

**Table 2 T2:** Reasons for canceling fresh embryo transfer.

Reasons	details
• High risks of OHSS	1. E2≥5000pg/ml or ≥18 follicles (GnRH-a trigger) on the trigger day; 2. E2≥1500pg/ml; 3. ≥18 oocytes obtained; 4. 1000pg/ml≤E2 ≤ 1500pg/ml on the day after OPU but the patient had mild OHSS symptoms.
• Endometrial and fallopian tube factors	1. Hydrosalpinx and intrauterine effusion occurred during COH; 2. Endometrial thickness ≤6mm on ET day; 3. Single endometrial polyps >10mm or multiple endometrial polyps (regardless of size);
• High progesterone level	1. blood progesterone level ≥1.5ng/ml on the trigger day; 2. blood progesterone level ≥1ng/ml for three consecutive days during the COH.
• Embryo factor	No high-quality day 3 embryos for transfer
• Patients’ factor	Patients request cancellation of fresh embryo transfer

OHSS, ovarian hyperstimulation syndrome; E2, estradiol; OPU, oocytes pick-up; COH, controlled ovarian hyperstimulation.

For patients who meet the criteria for fresh embryo transfer, they would receive vaginal progesterone sustained-release gel (Crinone^®^, Merck Serrano, Germany) 90mg per day or progesterone soft capsules (Utrogestan^®^, Besin, Belgium) 200mg per day plus dydrogesterone tablets (Duphaston^®^, Abbott, USA) 10mg twice a day for luteal support from the day after the OPU. All patients would undergo ET mediated by TVS. β- hCG would be detected 14 days after ET, and pregnant patients would continue to be given luteal support. After 2 weeks, the dosage of luteal support drugs would be gradually reduced in patients with at least one intrauterine gestational sac and heart tube beating by TVS. Luteal support drugs will be discontinued at 10 weeks of gestation.

#### Collection of endometrium

2.2.3

For patients who received the rhCG trigger and canceled fresh embryo transfer, endometrium could be collected if there were no obvious endometrial abnormality, OHSS and no elevated progesterone level. After the attending doctor communicates with the patient and fully informs the patient of relevant matters, the patient can voluntarily choose whether to take endometrial sampling.

For patients with endometrium collection who were determined to freeze whole embryos on trigger day, dydrogesterone tablets (Duphaston^®^, Abbott, USA) 10mg twice a day would be given for luteal support; For patients with endometrium collection who decide to freeze whole embryos after OPU, discontinue the use of Crinone^®^ (Merck Serrano, Germany).

Endometrium collection would be performed in all eligible patients on day 5 after OPU. A small amount of endometrial tissue would be obtained and rinsed with physiological saline. The endometrial tissue would be rapidly frozen in liquid nitrogen and stored in the refrigerator at -80°C for a long time.

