##### Depot GnRH-a protocol group

2.2.1.1

The patient would be given a subcutaneous injection of 3.75mg leuprorelin (Biote Pharmaceutical, Beijing, China) or 3.75mg triptorelin (Dophereline^®^, Ipsen, France/Decapeptyl^®^, Ferring, Switzerland) after endometrial thickness was determined to be <5mm with no follicle growth by transvaginal ultrasonography (TVS) on day 2 of the previous menstrual cycle. Approximately 28 days after injection, the patient would be confirmed to have reached the pituitary down-regulation position (E2 ≤30pg/ml and LH ≤2IU/L). Recombinant follicle-stimulating hormone (rFSH, Genescience Pharmaceutical, Changchun, China) would be selected for COH. The initial dose would be selected by the attending doctor according to the patient’s age, BMI, and ovarian reserve, and the dosage would be 150-225IU per day. During COH, doctors are allowed to adjust the dosage of Gn according to the patient’s ovarian response, and the maximum daily dosage would not exceed 450IU. When patients have a slow ovarian response during COH, human menopausal gonadotropin (HMG) (Lizon Pharmaceutical, Zhuhai, China) is allowed, and the dosage is determined by the attending doctor. During COH, any other adjuvant drugs are not allowed. When patients have two dominant follicles ≥18mm or three follicles ≥17mm in diameter, they would be triggered with recombinant human chorionic gonadotropin (rhCG, Ovidrel^®^, Merck Serono, Germany).

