### Strengths and limitations

3.1

Our study has several strengths. First, our RCT design could lead us to excavate the association between GH and pregnancy outcomes and endometrial receptivity and provide solid evidence for exploring the possible mechanisms. The GnRH-ant protocol is widely used in the world. Our results would provide a feasible method to solve the problem of poor pregnancy outcomes in patients receiving fresh embryo transfer with COH through GnRH-ant protocol and provide a basis for updating ART guidelines. Second, this RCT study designed by a multidisciplinary team of reproductive medicine clinicians, physicians, sonographers, statisticians, scientists, and other related experts, and multidisciplinary collaboration will guarantee the quality of research.

The main limitation of this study is the single-center study design in Hubei Province, China, without other reproductive medicine centers participation. In addition, the sample size is relatively small because it is a pilot study. Therefore, we will further confirm our conclusion by supplementing the results of relevant *in vitro* research.

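### The rhCG condition for endometrial donors bars trigger-day high-risk women in both antagonist arms but not in the depot arm, and no tissue comparison is protected by randomisation

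*Protocol article*

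**What the plan says.** Protocol article, section 2.2.3 (Collection of endometrium): tissue comes only from women with an rhCG trigger whose fresh transfer was cancelled: "For patients who received the rhCG trigger and canceled fresh embryo transfer, endometrium could be collected if there were no obvious endometrial abnormality". In full, the further condition is "no obvious endometrial abnormality, OHSS and no elevated progesterone level", and "the patient can voluntarily choose whether to take endometrial sampling".

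The trigger rule depends on the arm:

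- **Depot GnRH-a (2.2.1.1).** Once the follicle criterion is met, "they would be triggered with recombinant human chorionic gonadotropin". No alternative is stated for high OHSS risk.
- **Antagonist control (2.2.1.2).** The rhCG "trigger would be used if the patient is not at high risk for OHSS". The other branch begins "If the patient is at high risk for OHSS (trigger day E2≥5000pg/ml or ≥18 follicles with a diameter larger than 14mm"; these women get GnRH-a, or HCG 2000 IU with GnRH-a.
- **Antagonist plus GH (2.2.1.3).** "Based on the GnRH-ant protocol control group, all patients will receive subcutaneous injection of 5IU GH", so the control arm's trigger rule carries over.

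Table 2 lists the reasons for cancelling fresh transfer. Under high risk of OHSS it has a trigger-day item tied to the GnRH-a trigger, and later items that can follow an rhCG trigger in any arm (E2≥1500 pg/ml, or at least 18 oocytes). Section 2.2.4.1 sequences five tissues per group. Section 3.1 lists as a strength that "our RCT design could lead us to excavate the association between GH and pregnancy outcomes and endometrial receptivity".

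**The concern.** Donor eligibility depends on the trigger received, and the trigger depends on the arm. The same woman, above the threshold on trigger day, can become a donor if allocated to depot GnRH-a but not if allocated to either antagonist arm. A difference between depot and antagonist tissue in the receptivity markers could then partly reflect very-high-response cycles being admitted in one arm only.

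Separately, donors in all arms are defined by events after allocation: cancellation, OHSS, progesterone, and consent given in an open-label trial. Randomisation makes the 40 women per arm comparable, but not the subset who end up giving tissue. Endometrial receptivity is part of the stated aim and hypothesis, and section 3.1 relies on the randomised design for it and says that the in vitro results will help to confirm a conclusion drawn from a small sample.

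**Working it through.** **1. The one figure attached to the comparison.** Section 2.2.4.1: 3 groups × 5 tissues = 15, as stated. The point itself concerns a selection rule, so the main check is to follow a patient through the sections.

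**2. A woman above the trigger-day threshold, without OHSS or raised progesterone, whose transfer is cancelled.**

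| Arm | Trigger | Meets the rhCG condition? | Can donate? |
|---|---|---|---|
| Depot GnRH-a | rhCG | Yes | Yes |
| Antagonist control | GnRH-a, or HCG 2000 IU + GnRH-a | No | No |
| Antagonist + GH | As control | No | No |

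In the depot arm she can be cancelled under Table 2's later items (E2≥1500 pg/ml or at least 18 oocytes). The table reads HCG 2000 IU plus GnRH-a as not being an rhCG trigger; section 2.2.3 does not say so expressly.

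**3. A woman below the threshold.** She gets rhCG in all three arms. If a later Table 2 item cancels her transfer, she is eligible everywhere on the same terms. The asymmetry is confined to the trigger-day threshold.

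**4. Possible size (illustrative).** The documents give no rate of high risk or of cancellation. Assume, for the depot arm:

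- h = share of women above the threshold on trigger day, 5% to 20%
- r = share of those who are cancelled and free of OHSS, 25% to 80%
- c = share of the other women who are cancelled and eligible, 10% to 30%

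The share of eligible depot donors who were above the threshold is s = h·r / [h·r + (1−h)·c].

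- Low: 0.05×0.25 / (0.05×0.25 + 0.95×0.30) = 0.0125 / 0.2975 = 4%
- Middle: 0.10×0.50 / (0.10×0.50 + 0.90×0.20) = 0.05 / 0.23 = 22%
- High: 0.20×0.80 / (0.20×0.80 + 0.80×0.10) = 0.16 / 0.24 = 67%

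In both antagonist arms s = 0 under the rule. If s = 20%, the chance that five depot tissues include at least one such woman is 1 − 0.8⁵ = 67%.

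**5. Effect on a marker test.** Assume a marker differs by 1 SD between women above and below the threshold, and that there is no true arm difference. The expected spurious depot-antagonist gap is s × 1 SD. In a simulation of a two-sample t test with five per arm (200,000 replicates, nominal 5%), the false-positive rate was:

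| s | Spurious gap (SD) | False-positive rate |
|---|---|---|
| 4% | 0.04 | 5.1% |
| 10% | 0.10 | 5.2% |
| 22% | 0.22 | 5.9% |
| 40% | 0.40 | 8.3% |

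With five tissues per arm the inflation is slight unless s is large.

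**The case against.** **The GH question is untouched by the trigger asymmetry.** The trial asks what GH does in antagonist cycles. GH and control share the same trigger and donor rules. This stands: the asymmetry affects only comparisons with the depot arm.

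**Women with OHSS are already excluded.** This narrows the gap, because depot women who develop OHSS cannot donate. If section 2.2.3 meant high risk of OHSS, as Table 2's heading has it, the asymmetry would largely disappear. The text names OHSS, however, not risk of it, so read literally high-risk depot women without OHSS remain eligible.

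**The size may be small.** The population is normal responders with PCOS excluded, so crossing the threshold may be uncommon. This stands; no rate is given either way.

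**Selection after allocation is unavoidable.** Tissue cannot be taken from a woman who has just had a fresh day-3 transfer, so donors must come from cancelled cycles. The rhCG condition also has a merit: it holds trigger type constant across donors. The article calls the mechanistic work preliminary, and the markers are not listed among the primary or secondary outcomes. All of this is fair and limits the importance of the point. It does not support crediting the randomised design for receptivity evidence in section 3.1.

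**A stronger reading about GH.** A reader might infer that GH itself shifts who becomes a donor, because the Introduction credits it with better ovarian response and oocyte quality. That passage links those effects to improved outcomes in older women and poor responders. A shift in normal responders is possible, but the documents do not show it.

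**Conclusion.** The point holds in a limited form. As written, the rhCG condition excludes trigger-day high-risk women from tissue donation in both antagonist arms and excludes nobody in the depot arm. This rests on two readings: that HCG 2000 IU plus GnRH-a is not an rhCG trigger, and that the OHSS exclusion means OHSS and not risk of it.

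The depot-versus-antagonist tissue comparison is therefore asymmetrically selected, by an amount the documents do not allow anyone to estimate. The 4% to 67% range and the 1 SD marker shift are assumptions. A reader might infer a badly inflated false-positive rate; at five tissues per arm the calculation does not support that at low or middle values of s.

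GH versus antagonist control does not share this asymmetry, but it is not a randomised comparison either, since every remaining condition for donation arises after allocation. The primary outcome is unaffected. What needs correcting is one eligibility rule and one claim of strength.

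**What to change.** - **Section 2.2.3**, for tissue sampling only and with no change to treatment: keep the rhCG condition and add that, in every arm, a woman who met the trigger-day threshold (E2≥5000 pg/ml or ≥18 follicles >14 mm) is not a tissue donor. This also settles the case of HCG 2000 IU plus GnRH-a.
- **Reporting**: give donors' trigger-day E2, progesterone and cancellation reason by arm.
- **Sections 2.2.4 and 3.1**: state that the tissue comparison is exploratory and non-randomised, and stop crediting the RCT design for the receptivity evidence.

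Balancing donors on cancellation reason is not advised. The reason itself arises after randomisation, so balancing on it would not restore comparability, and with five donors per arm it may not be feasible.

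The cost is wording, a short descriptive table and slightly fewer eligible depot donors. No new procedure is needed.

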#### Endometrium research

2.2.4

For the obtained endometrium samples, the following *in vitro* studies and tests would be performed:

##### Transcriptome analysis of endometrial tissues

2.2.4.1

RNA would be extracted from 5 endometrial tissues in each group (15 endometrial tissue samples in total) by Trizol, and eukaryotic reference transcriptome would be detected by next-generation sequence (NGS), and subsequent bioinformatics analysis would be performed by R software. The obtained results would be verified by real-time quantitative PCR (qRT-PCR).

##### Endometrial receptivity molecular detection

2.2.4.2

qRT-PCR and Western blotting would be used to detect the expression of mRNA and protein levels of endometrial receptivity and decidualization molecules, including LIF, integrinβ3, S100P, HOXA10, SCARA5, DIO3, FoxO1, etc (23–26).

#### Follow-up plan

2.2.5

Patients would be followed on enrollment day, trigger day, ET day, 7 days after OPU, 15 days after ET, 28 days after ET, and 12 weeks of gestation (**Table 3**).

**Table 3 T3:** Overview of follow-up during the study.

Time	Follow-up Information
• Enrollment day	Patient randomization, collection of baseline characteristics of the participants (age, body mass index, primary infertility/secondary infertility; infertility duration; cause of infertility, history of fertility treatment; past medical history; history of drug allergy; vital signs; physical examination; urine hCG test; electrocardiogram; basal FSH, LH, E2, PRL, T, P, AMH, AFC; blood routine; urine routine; blood biochemistry; coagulation function; blood type; hepatitis B, syphilis, HIV examination, etc.).
• Trigger day	LH, E2, P levels; TVS; GH medication records; rFSH medication record; GnRH-ant medication record; HMG medication record; rhCG or GnRH-a medication record; untoward reaction record.
• ET day	Oocytes status; embryo status; luteal support medication record; number and morphological evaluation of transferred embryos; untoward reaction record.
• 7 days after OPU	Blastocysts status, collection of endometrium samples; untoward reaction record.
• 15 days after ET	serum β-hCG levels; luteal support medication record; untoward reaction record.
• 28 days after ET	TVS; luteal support medication record; untoward reaction record.
• 12 weeks of gestation	Pregnancy outcomes (ongoing pregnancy rate or early miscarriage or ectopic pregnancy); untoward reaction record.

hCG, human chorionic gonadotropin; FSH, follicle stimulating hormone; LH, luteinizing hormone; E2, estradiol; PRL, prolactin; T, testosterone; P, progesterone; AMH, anti-mullerian hormone; AFC, antral follicle count; HIV, human immunodeficiency virus; TVS, transvaginal sonography; GH, growth hormone; HMG, human menopausal gonadotropin; OPU, oocytes pick-up; ET, embryo transfer.

### Primary outcomes

2.3

The primary outcome is the ongoing pregnancy rate (OPR). OPR was defined as a clinical pregnancy until after 12 weeks of gestation.

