## Introduction

1

With the rapid development of assisted reproductive technology (ART), seeking an efficient and safe ovarian stimulation protocol is the main pursuit of doctors worldwide. Gonadotropin-releasing hormone agonist (GnRH-a) protocol, gonadotropin-releasing hormone antagonist (GnRH-ant) protocol, progesterone primed ovarian stimulation (PPOS) protocol, and minimal ovarian stimulation protocol are commonly used worldwide. The GnRH-ant protocol has received global attention for its simplified treatment course, shortened treatment period, and low incidence of ovarian hyperstimulation syndrome (OHSS) (1, 2). In 2020, the European Society of Human Reproduction and Embryology (ESHRE) published guidelines for controlled ovarian hyperstimulation (COH), indicating that GnRH-ant protocol can be used as first-line treatment for patients with high, normal, or poor ovarian response (3). Considering the safety of COH, ESHRE guidelines strongly recommended GnRH-ant protocol as a prior treatment for normal ovarian response (NOR) patients (3, 4).

For patients with NOR, the ideal therapeutic goals are to reduce the duration of COH, shorten the time to live birth and improve the pregnancy rate of fresh embryo transfer (1). However, previous studies have demonstrated that pregnancy outcomes of fresh embryo transfer with GnRH-ant protocol are not ideal. A retrospective study involving 203,302 fresh embryo transfer IVF cycles revealed a significantly higher cycle cancellation rate and a significant lower implantation rate and clinical pregnancy rate on the GnRH-ant protocol compared with those on the GnRH-a protocol (5). Another retrospective study indicated that the clinical pregnancy rate and live birth rate of patients receiving fresh embryo transfer with GnRH-ant protocol were significantly lower than those of frozen embryo transfer (6).

In recent years, how to promote the pregnancy rate of fresh embryo transfer with GnRH-ant protocol has become a research hotspot. Several studies have shown that serum luteinizing hormone (LH) levels, progesterone levels, trigger methods, and the method of GnRH antagonist usage during COH are associated with adverse pregnancy outcomes, but there is still a lot of controversy (7–13).

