Growth hormone (GH) is a single-chain polypeptide hormone secreted by the anterior pituitary eosinophilic cells, consisting of about 190 amino acids. It has been more than 30 years since GH was first reported to be applied in the field of ART in 1988 (14). Current studies have shown that GH can regulate primordial follicle development, improve ovarian response to gonadotropin (Gn), improve oocyte quality, improve oocyte and granulosa cell mitochondrial function and oxidative stress state, and thus improve the pregnancy outcome of elderly women and patients with poor ovarian response (POR) (15). A meta-analysis consisting of 15 randomized controlled trials (RCTs) involving 1448 patients with POR found that GH can significantly increase the live birth rate, clinical pregnancy rate, and the number of oocytes retrieved, while significantly reducing the cycle cancellation rate and Gn dosage (16). Expert consensus on clinical diagnosis and treatment of POR patients in China points out that GH is recommended during the ART process for patients with POR, low embryo quality, thin endometrium, and recurrent implantation failure (RIF) (17). The guidelines also explicitly suggest the possibility of GH in improving endometrial receptivity.

A recent meta-analysis involving 17 RCTs found that GH supplementation may benefit patients with POR by improving endometrial thickness, clinical pregnancy rate, and live birth rate (18). Some studies have also confirmed that GH can improve pregnancy outcomes for patients with thin endometrium and RIF (19, 20). Besides, a single-center retrospective study including 80 patients who received GH treatment for POR or low fertilization rate or low blastocyst formation rate in the previous cycle found that GH can significantly increase the endometrial thickness without significant side effects or untoward reaction (21). However, no prospective study has confirmed the efficacy of GH in fresh embryo transfer with GnRH-ant protocol, and its potential mechanism has not been studied. This study intends to enroll NOR patients receiving fresh embryo transfer with GnRH-ant protocol to evaluate whether GH supplementation can improve the pregnancy outcome of fresh embryo transfer, and preliminarily explore the possible mechanism.

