### Secondary outcomes

2.4

The secondary outcomes in this study include the Gn dosage, duration of COH, endometrial thickness and pattern, LH, E2, P level on trigger day, numbers of retrieved oocytes, high-quality embryo rate, biochemical pregnancy rate, clinical pregnancy rate, implantation rate, ectopic pregnancy rate, early miscarriage rate, multiple pregnancy rate and incidence of moderate and severe OHSS. The high-quality embryo was defined as embryos with 7-10 cells of 2PN origin and blastomere fragments ≤20% on day 3 after fertilization (22). Biochemical pregnancy was defined as a serum level of β-hCG of more than 10 mIU per milliliter (27). Clinical pregnancy was determined when at least one gestational sac was observed on TVS. Early miscarriage was defined as pregnancy loss before 12 weeks of gestation.

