### Sample size calculations

2.5

According to the previous literature review, no study has reported whether GH can improve the ongoing pregnancy rate of patients undergoing fresh embryo transfer with GnRH-ant protocol. Combined with the data of our center, the ongoing pregnancy rate of patients receiving fresh embryo transfer under GnRH-ant protocol was about 51.5%, and that of patients receiving depot GnRH-a protocol was about 69.7% (unpublished), while GH could increase the ongoing pregnancy rate by about 12%. The sample size was estimated using the chi-square test with α=0.05 and 1-β=0.8, then we need about 133 people per group, considering 10% shedding, about 147 people per group are needed.

Considering that this study is a pilot study designed to initially evaluate the feasibility, safety, efficacy, and range of variation of the GH intervention. Based on the above considerations, one-third to a quarter of the estimated sample size was selected for the pilot study, 40 patients are included in each group, and 120 patients would be expected to be recruited for this study.

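### The primary ongoing pregnancy rate has no stated denominator, and the one population attached to it, patients receiving fresh transfer, is formed after randomisation

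*Protocol article*

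**What the plan says.** **Outcome.** Section 2.3 names the ongoing pregnancy rate (OPR) as primary and defines the event: "OPR was defined as a clinical pregnancy until after 12 weeks of gestation". It gives no denominator. Section 2.6 names a chi-square test and a logistic regression for OPR, again without saying which patients are counted.

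**Planning rates.** Section 2.5 states that "the ongoing pregnancy rate of patients receiving fresh embryo transfer under GnRH-ant protocol was about 51.5" percent, and "that of patients receiving depot GnRH-a protocol was about 69.7% (unpublished"). The first figure is explicitly for fresh-transfer patients. The second, for the depot agonist, carries no explicit transfer denominator.

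**Timing.** The enrolment-day row of Table 3 (section 2.2.5) reads "Patient randomization, collection of baseline characteristics of the participants". Section 2.2.2 then provides "For patients who need to cancel fresh embryo transfer due to various reasons", and Table 2 lists the reasons: high OHSS risk (estradiol, follicle or oocyte count), endometrial or tubal findings, raised progesterone, no high-quality day 3 embryo, and patient request.

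**Evidence on cancellation.** The Introduction cites a retrospective study that "revealed a significantly higher cycle cancellation rate and a significant lower implantation rate and clinical pregnancy rate on the GnRH-ant protocol" compared with the agonist protocol. It also cites a meta-analysis in poor responders in which growth hormone (GH) raised pregnancy and live birth rates "while significantly reducing the cycle cancellation rate and Gn dosage".

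**The concern.** A rate without a denominator leaves the primary comparison open. Here the choice matters because whether a patient has a transfer is settled after allocation.

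Several Table 2 criteria use variables that section 2.4 lists as secondary outcomes to be compared between arms: trigger-day estradiol and progesterone, oocyte number, endometrial thickness and high-quality embryo rate. The plan therefore allows that treatment may move the variables that decide who is transferred. Patient request is a further route, and patients know their arm (section 2.2).

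If OPR were computed among transferred patients only, the groups compared would no longer be the groups randomised. A difference could then arise from who was transferred, and a real one could be hidden. If the denominator is left open until results are seen, it can also be chosen with the results in view. Finally, per-transfer planning rates do not describe the 40 patients randomised per arm unless nobody is cancelled.

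**Working it through.** **1. Reproducing the plan's sample size.** Inputs from section 2.5: 51.5% (antagonist), 69.7% (depot agonist), a GH gain of about 12%, read here as 12 percentage points (63.5%), α = 0.05, power 80%. The test is read as a three-group chi-square with 2 degrees of freedom.

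- Mean rate = (0.515 + 0.635 + 0.697)/3 = 0.6157.
- Effect size w² = mean squared deviation / [0.6157 × (1 − 0.6157)] = 0.02412.
- Total N for 80% power = 399.4, or 133.1 per group. The plan says 133.
- Allowance for loss: 133 × 1.1 = 146.3, rounded up to 147. The plan says 147. (133/0.9 would give 148.)

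The 133 is obtained by applying the stated rates to every patient counted, with no reduction for cancelled transfers.

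**2. Is cancellation expected?** Section 2.2.3 takes endometrium only from patients whose fresh transfer was cancelled, and section 2.2.4.1 needs 5 samples per group. If these come from the randomised patients, that is at least 5/40 = 12.5% per group. Section 2.2.3 does not sample patients with an obvious endometrial abnormality, OHSS or raised progesterone, so cancellations with those features would be additional.

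**3. From per transfer to per randomised.** With cancelled fraction c and no fresh-cycle pregnancy in cancelled patients, per-randomised OPR = per-transfer OPR × (1 − c). The documents give no c, so the values below are assumptions. The last column repeats step 1 with all three rates multiplied by (1 − c).

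| c, equal in all arms | Transfers from 40 | 51.5% per transfer becomes | n per group, three-group test |
|---|---|---|---|
| 0% | 40 | 51.5% | 133 |
| 10% | 36 | 46% | 172 |
| 20% | 32 | 41% | 220 |
| 30% | 28 | 36% | 282 |
| 40% | 24 | 31% | 364 |

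**4. Unequal cancellation (assumed).** Let both arms have a true per-randomised OPR of 40%, that is 16 ongoing pregnancies among 40. With 20% cancelled in one arm and 30% in the other:

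- 16/32 = 50.0% per transfer
- 16/28 = 57.1% per transfer

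The 7.1-point difference appears although both arms produced the same number of pregnancies per woman randomised. Conversely, suppose a 12-point per-transfer gain (51.5% to 63.5%) with 20% cancelled in control. The per-randomised difference is zero when 0.635 × (1 − c) = 0.515 × 0.8, so c = 1 − 0.412/0.635 = 35% in the GH arm.

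**5. Direction.** Take an illustrative mixture: 65% of women with OPR 62% and 35% with OPR 30%, with GH only cutting cancellation from 30% to 20%.

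| Who is cancelled | Per transfer | Per randomised |
|---|---|---|
| Poorer-prognosis women | 59.7% → 56.0% | 41.8% → 44.8% |
| Better-prognosis women | 46.0% → 48.0% | 32.2% → 38.4% |

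The two measures disagree in sign in the first pattern and agree in the second.

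**The case against.** The strongest reply is that nothing commits the trial to a per-transfer analysis. Section 2.6 names no exclusions, and analysis sets are often left to a full protocol or SAP, which is not shown. It is right that a per-transfer analysis is inferred, and only the missing denominator is documented. But the denominator is part of the definition of a primary rate. This article gives that definition, leaves it incomplete, and offers one cue, which points to transferred patients.

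Second, a reader might infer that GH is known to lower cancellation here. The documents do not support that. The GH finding is in poor responders, while this trial enrols normal responders aged 20–35 and excludes thin endometrium. Both cited findings concern cycle cancellation, which the article does not equate with cancelling a fresh transfer under Table 2. They show plausibility, not size. Most Table 2 criteria are also numeric thresholds, and embryologists and laboratory technicians are blinded, so patient request is the clearly discretionary route.

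Third, a reader might infer that the two measures must point in opposite directions. Step 5 shows that this depends on who is cancelled. Table 2's first category, high OHSS risk, is not obviously a poor-prognosis group.

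Fourth, because "Clinical pregnancy was determined when at least one gestational sac was observed on TVS", a reader might infer that a non-viable sac could count as ongoing. The 12-week follow-up in Table 3 classifies pregnancies as ongoing, miscarried or ectopic, and section 2.4 defines early miscarriage as loss before 12 weeks. That largely answers the point, and it is not pressed.

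The pilot status lowers the weight of the sample size consequences: 40 per arm is a chosen fraction, and the 10% loss allowance, which the article does not define, enters only the 147. It does not remove the bias question, since efficacy is a stated pilot aim and OPR is compared at two-sided p<0.05.

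**Conclusion.** The point holds in this form: the primary rate lacks a denominator, the only population explicitly attached to it is formed after randomisation, and the criteria forming it include variables the trial compares between arms. A per-transfer primary comparison could therefore be biased. Whether it would be, by how much and in which direction cannot be determined from the documents, because they give no cancellation rate by arm.

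The sizes shown rest on assumed cancellation of 10% to 40%, and on counting a patient without a fresh transfer as having no ongoing pregnancy from that cycle. Within that range the denominator alone moves the control rate from 51.5% to between 46% and 31%, and a 10-point imbalance in cancellation can produce a 7-point per-transfer difference with no difference per randomised patient. The assumed GH effect is 12 points. The 69.7% is read as per transfer only because it shares a sentence with the 51.5%. The denominator should be fixed before outcome data are compared.

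**What to change.** - **Section 2.3:** define the primary OPR as ongoing pregnancies from the fresh cycle divided by all patients randomised to the arm, counting a patient without a fresh transfer as no ongoing pregnancy.
- **Sections 2.4 and 2.6:** report per-transfer OPR as a secondary outcome, with the cancellation rate and reasons by arm. Name all randomised patients as the population for the chi-square test and logistic regression of the primary outcome.
- **Section 2.5:** either restate the planning rates and the 133 and 147 per randomised patient, using the centre's own cancellation data, or say that they apply to transferred patients only. Give the denominator of the 69.7%.

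The cost is wording in four subsections. The outcome data are already planned, and cancellation reasons have to be established to apply Table 2. The downside is lower expected rates, and a larger number needed for the same power in any later full-scale trial. The pilot's 40 per arm need not change.
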